### Intervention: the CAPRI program

Throughout the course of the study, participants from the control group will receive their care as usual, while participants from the intervention group will benefit, for 6 months, from the CAPRI program alongside the usual treatment, comprising a monthly visit to the referring oncologist at Gustave Roussy (mainly for prescription renewal). Both groups will receive oral chemotherapy and/or targeted therapy prescribed at Gustave Roussy, as well as regular check-ups for other treatments.

#### Nurse navigators

Two Nurse Navigators ensure patient follow-up at a distance, via phone interviews and email, from Monday to Friday, during office hours only (9 am to 5 pm). Patients benefit from regular follow-up by phone. Calls will be scheduled as follows: once a week during the first month, once every two weeks from the second to the fourth months and once every three weeks from the fifth month to the end of the study.

Nurse Navigators provide the link between the hospital professionals, patients and primary care professionals (GP, private nurse, pharmacist, etc.) given access to the web portal following patient agreement.

#### Web portal

The web portal provides a unique interface through which healthcare professionals are able to connect with their patients. Each program stakeholder has his/her own login for access to a tailored portal; Table 1 presents its main functionalities.

**Table 1 Tab1:** Description of the main functionalities of the CAPRI web portal

Functionalities	Description
Messages	Secured message facility for contacting NNs
Follow-up	Tracking of follow-up measures (temperature, weight, pain, appetite) and if necessary, self-reporting of other symptoms
Schedule	Displays and saves appointments on a personal schedule
Address book	Provides access to an address book containing the addresses and phone numbers of professionals enrolled, as well as other useful numbers
Information	Provides access to reference websites providing information about the disease, treatment options and their side effects
Storage	Downloads, saves and files documents relating to patient care (clinical and biological exams, patient records, etc.)
Reminders	Schedules reminders to take medications, arrange appointments, plan exams, and document personal measurements

The web portal provides NNs with a dashboard so that they can monitor the records of all patients enrolled in the program. Following each contact with a patient, NNs can create ‘intervention reports’ detailing what they have done or discussed, and transmit the information to those professionals previously indicated by the patient in question. These professionals can log on the portal to communicate with NNs online and access information regarding the patients they care for (following patient agreement).

The system also generates automatic alerts to patients or NNs. Alerts and patient requests can be generated in various ways:automatically, through the web portal, for instance while reporting follow-up measures (if the patient measures are below or above predefined thresholds)by the NNs during regular follow-upsby a message/call of the patient or the professionals.

The NN evaluates the alert level on the basis of algorithms (NCI-CTCAE classification) and determines the action to implement, in line with navigation algorithms. Depending on level, the NN can give advice, refer the patient to their primary care physician or to a professional at Gustave Roussy, or contact the dedicated services to organize a hospitalization or schedule an appointment for the patient.

### Impact evaluation

#### Primary endpoint

The primary endpoint of the study will be significant change in the delivery of oral treatment, measured by Relative Dose Intensity, which is calculated as the ratio of the dose actually delivered over time to the prescribed dose intensity. Our hypothesis is that, thanks to faster management of treatment side effects, patients in the CAPRI program will demonstrate a significant increase in Relative Dose Intensity, in comparison with those from the control group.

#### Secondary endpoints

Secondary endpoints will be patient adherence to oral anticancer therapy, quality of life (functional scales, symptom scales, global health status and quality-of-life scales), patient experience, tumor response, Progression Free Survival (PFS), Overall Survival (OS) and toxic side effects of the therapy (severity and quantity). We expect that patients in the intervention arm, by comparison with controls, will demonstrate significantly greater improvements in secondary outcomes measures. Demographic, socio-economic and clinical variables will be assessed and considered in order to adjust the study results. These adjustment factors could be used to make stratified group comparisons.

#### Instruments of measurement

Outcomes will be assessed by a Clinical Research Associate (ARC) at baseline, and each month until the end of the program (after 6 months), excepted for patient quality of life (at baseline, after 3 months and at the end of the program) and for patient experience (at the end of the program). Instruments used to collect data from participants, including primary and secondary outcomes, are listed in Table 2.

**Table 2 Tab2:** Variables and Instruments used for data collection

Measurement tools ARC administered (face to face interview)		Time point			
		At baseline	Each month	After 3 month	After 6 months
Demographics and general medical history	Age, gender, comorbidities	*			
Socioeconomic status	Education, income, employment, family characteristics	*			
Diagnosis	Cancer type, stage	*			
Autonomy	OMS score [55]	*	*	*	*
Treatment Delivery	RDI ratio [30] Morisky questionnaire [56] MEMs (only for targeted therapy) [57]		*	*	
Toxic effects	NCI-CTC-AE (CTCAE v4.0)		*	*	
Overall Survival	OS		*		
Progression Free Survival	PFS		*		
Tumor response	RECIST [58]		*		
Quality of life	EORT QLQ-C30 [59]	*		*	
Patient experience Satisfaction	PACIC [60]				*

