### Participants

Recruitment will take place at the Gustave Roussy Comprehensive Cancer Center and will be open to patients with metastatic cancer taking oral chemotherapy and/or targeted therapy. 1,000 patients initiating oral therapeutics will be recruited. Recruitment will be managed by the referring department at Gustave Roussy.

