### Data analysis

Appropriate descriptive statistics will allow presentation and comparison of sample characteristics at baseline, and at each evaluation time point. The primary analyses will utilize a between-group design (CAPRI versus control groups) at six time points (each month)). Significant change in treatment delivery will be measured on the RDI ratio, calculated with the Morisky score and/or the Medication Event Monitoring System (MEMs) results. If distribution is normal, a student *t*-test will be used to compare RDI means, as well as secondary outcomes designed as continuous variables. If not, a Mann–Whitney test will be used. Chi2 or Fisher’s test will be used to compare secondary outcomes designed as binary variables. Baseline data will be examined to analyze probability of attrition bias.

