### Study advantages and disadvantages

Assessing delivery of oral anticancer therapy through measurement of both medication adherence and Relative Dose Intensity needs rigorous methods. Based on the results of previous studies [6], we decided to use the RDI measure using a self-reported questionnaire (Morisky), combined with a MEMs for patients receiving targeted therapy. This two-fold strategy should enable us to avoid the risk of adherence overestimation for psychological reasons (shame, guilt) [4, 39]. It has been presented as the most relevant strategy for measuring medication adherence [40] when the use of objective methods (such as blood sampling) is not possible.

The implementation of a medico-economic evaluation nested within our study is innovative; to our knowledge, evaluations of navigation programs in oncology targeting the treatment phase have been scarce [41]. Economic evaluations are encouraged by experts in this field [42] since they allow us to formulate policy and resource allocation implications, such as the development of financial incentives to improve care coordination. Improving patient adherence to oral anticancer therapy and improving their Relative Dose Intensity via a navigation program combined with Health Information Technology - is challenging for the organization of healthcare. Indeed, improved adherence to oral treatment would probably favor community care for patients with cancer, which would in turn imply reduced unplanned activity for hospitals and increased activity for community cancer care. Changes in patient follow-up will generate a need to better inform (train) community care professionals (which could be supported by a navigation program offering a web portal for professionals, as CAPRI does) [43] and adaptation of the payment system to this new care organization, which requires increased coordination between primary and secondary care [44].

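### For patients on oral chemotherapy alone, adherence rests on a Morisky listed as asked face to face, so the protection claimed against shame-and-guilt overestimation does not reach them

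*Protocol article*

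**What the plan says.** All of the following is in the protocol article.

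- **Instruments of measurement, text:** "Outcomes will be assessed by a Clinical Research Associate (ARC) at baseline, and each month until the end of the program (after 6 months". Quality of life and patient experience follow their own timing.
- **Instruments of measurement, Table 2:** a single header, "Measurement tools ARC administered (face to face interview", stands over every row. The Morisky, QLQ-C30 and PACIC are all below it. The treatment-delivery row restricts electronic monitoring: "MEMs (only for targeted therapy".
- **Study advantages and disadvantages:** "we decided to use the RDI measure using a self-reported questionnaire (Morisky), combined with a MEMs for patients receiving targeted therapy". The next sentence gives the purpose: "This two-fold strategy should enable us to avoid the risk of adherence overestimation for psychological reasons (shame, guilt".
- **Data analysis:** the RDI ratio is "calculated with the Morisky score and/or the Medication Event Monitoring System (MEMs) results".
- **Participants:** recruitment is open to "patients with metastatic cancer taking oral chemotherapy and/or targeted therapy", so patients on oral chemotherapy without a targeted agent are eligible.

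**The concern.** A question about missed doses put by a study associate across a table is a setting in which shame and guilt are likely to act. The plan names that bias and says its measurement strategy deals with it, but the strategy depends on an electronic record that part of the trial population does not have. For that part, the mode shown in Table 2 works against the stated aim and nothing listed would reveal the problem.

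More than a secondary adherence endpoint is at stake, because the Morisky is named as an input to the primary RDI. The trial cannot hide allocation from patients: the CAPRI group meets the navigators and receives portal access (Participant recruitment procedure; Randomization procedure), has scheduled calls (Nurse navigators) and can use medication reminders (Web portal, Table 1). The pressure to give a good answer may therefore differ between arms.

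**Working it through.** **1. Which patients does the stated protection cover?**

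| Treatment | Morisky | MEMs | Pairing described in the Discussion |
|---|---|---|---|
| Includes targeted therapy | listed, under the interview header | listed | present |
| Oral chemotherapy alone | listed, under the interview header | not used | absent |

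The second row follows from the restriction of MEMs in Table 2, repeated in the Discussion, together with the eligibility of oral chemotherapy in the Participants section. The article does not say what share of the 1,000 patients falls in that row.

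**2. Does the Morisky reach the primary endpoint?** Yes. The Data analysis section names the Morisky score and MEMs as the sources of the RDI ratio, joined by and/or. Where MEMs is absent, the Morisky is the only one of the two left. The article gives no conversion from Morisky score to RDI, so a shift on one scale cannot be translated into the other.

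**3. The plan's own figure.** Inputs from the Sample size calculation section: difference 5 points of RDI, SD 25, alpha 0.05 (two-sided assumed), power 80%.

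n per group = 2 × (1.960 + 0.842)² × 25² / 5² = 2 × 7.85 × 25 ≈ 392.4, rounded up to 393.

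This reproduces the stated 393 per group, so the sample size is not in question here.

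**4. How sensitive is the comparison to reporting that differs by arm?** The documents give no size for such a shift. The values below are assumptions, in points of RDI and on the whole-arm mean. They are not estimates.

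Standard error of the difference = 25 × √(2/393) ≈ 1.78.

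With no true effect and a differential shift b, the two-sided rejection rate is 1 − Φ(1.96 − b/1.78) + Φ(−1.96 − b/1.78):

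| Assumed shift b (RDI points) | Rejection rate |
|---|---|
| 0 | 5% |
| 1 | 8.7% |
| 2 | 20% |
| 3 | 39% |

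If over-reporting arose only in patients without MEMs, and they made up a share p of each arm, a whole-arm shift of b would need a shift of b/p among them. Since p is not given, the table shows only that small differential shifts would matter if they reached RDI. It does not show that they occur.

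**5. Equal over-reporting.** If both arms are inflated by the same amount, the shift cancels in the difference: b = 0, and the rejection rate stays at 5%.

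**The case against.** **The header may be a loose label.** It also covers MEMs, RECIST and overall survival, none of which comes from interviewing a patient. A form handed out and collected at the visit could sit under the same label, and the full protocol may give the mode for each instrument. This stands as a limit on certainty: one cannot be sure that the Morisky is read aloud. It does not remove the point, because the article states a mode. If that mode is not meant for the questionnaires, the table needs correcting anyway.

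**The Discussion does not contradict Table 2.** A reader might infer that calling the Morisky self-reported clashes with an interview. The text does not support that. Answers given to an interviewer are still self-report, and the Discussion rests its protection on the pairing with MEMs, not on how the Morisky is administered. For patients with MEMs the electronic check remains. What survives is the gap for patients without it.

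**The QLQ-C30 and PACIC.** A reader might infer that the plan undoes its own assurance for these too. It does not, because the assurance concerns adherence only. For these two the concern is ordinary social-desirability bias. Nor does the article say that the PACIC rates the CAPRI programme, or who employs the associate, so describing it as patients grading the hospital's programme to hospital staff goes beyond the text.

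**Self-completion does not blind anyone.** This stands. Patients would still know their group, so the fix reduces the pressure of answering in person but does not remove every source of differential reporting.

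**Conclusion.** The point holds in a narrow form. For patients on oral chemotherapy alone, the only adherence instrument listed is a Morisky that Table 2 places in a face-to-face interview. The protection described in the Discussion does not extend to them, and the instrument feeds the primary RDI.

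The size of any bias is unknown. A reader might infer that the results will be pushed in CAPRI's favour by some fraction of the 5-point target. The documents do not support this: they give neither a size nor a direction for differential over-reporting, and no link from Morisky points to RDI points. The conclusion rests on taking the table header at its word and on some enrolled patients having no targeted agent, which eligibility allows. It is a cheap improvement to make, not a flaw that invalidates the comparison.

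**What to change.** - **Table 2:** split the single header in two. Staff-collected: OMS score, CTCAE, RECIST, survival, dose and MEMs records. Patient-completed: Morisky, QLQ-C30 and PACIC.
- **Morisky:** have the patient complete it alone, before the interview, in the same way in both groups. The associate checks only that the form has been returned, and any help given is recorded.
- **QLQ-C30 and PACIC:** use the same procedure as a general precaution against social-desirability bias.
- **Study advantages and disadvantages:** limit the assurance about shame and guilt to patients who have MEMs, and say that for the others adherence is self-reported without an electronic check.

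The cost is small, since assessments at these time points are already planned and the article already uses self-questionnaires for monthly non-hospital costs. The downside is slightly more missing items than an interview would leave.

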### Economic evaluation

The economic evaluation of the CAPRI program will adopt a societal perspective, assessing intervention, medical and non-medical costs. All resources used by patients included in the study will be considered in the frame of a cost-effectiveness study. It is expected that in comparison with usual care, CAPRI intervention will result in cost-effective care with improvement in patients’ adherence to oral anticancer therapy. Cost data will be collected monthly using retrospective self-questionnaires for non-hospital costs. For hospital costs, medico-administrative data will be used. Table 3 presents the resources used to be included in the cost-effectiveness study, and their value units.

**Table 3 Tab3:** Resources used for the economic evaluation

Resources used		Value units
Medical resources		
Hospital	- Number and length of unplanned hospitalizations (by service department – specify which hospital) - Number and length of planned hospitalizations (by department service – specify which hospital) - Number of unplanned consultations in oncology - Number of planned consultations in oncology -Number of cancelled consultations (by service department – specify which hospital) - Number of consultations in supportive care (by type of supportive care service) -Reduction of supportive care treatment	Stay cost Stay cost Consultation tariff Consultation tariff Consultation tariff Consultation tariff Medication price
Non-hospital	-Number of GP consultations -Number of visits by private nurses -Number of consultations with other paramedical professionals	Consultation tariff Visit tariff Consultation tariff
Non-medical resources		
Transport	- Number of home-to-hospital journeys made (by transport type)	Travel cost
Professional care	-Hours of professional care (by task performed)	Hourly tariff
Informal care	-Hours of informal care	Hourly wage rate
Intervention		
	-Nurse Navigators training -Nurse Navigators wage -Web portal design and implementation -Office equipment (computer, phone, desk)	Hourly wage Hourly wage Web portal invoice + monitoring package Equipment price

### Process evaluation

A parallel evaluation will be conducted to describe both the steps taken to implement the intervention, and the prevailing conditions, which may be important to helping/supporting process implementation. This evaluation will be led as a longitudinal study through quarterly assessments of web portal use by enrolled patients and professionals, alongside evaluations of their satisfaction and needs. Analysis will also include the description of Nurse Navigator activities and specific skills. Data on access to, and use of, the web portal will be extracted from the web portal records. In addition, focus groups with Nurse Navigators will be organized throughout the study. Lastly, semi-structured interviews with patients, relatives and healthcare professionals engaged in the program will be conducted by the research team at the end of the trial. Combining a process evaluation with an outcome evaluation will provide a comprehensive evaluation of the CAPRI program [37]. It will also give important indications as to the sustainability of any improvement in quality achieved [38].

### Data analysis

Appropriate descriptive statistics will allow presentation and comparison of sample characteristics at baseline, and at each evaluation time point. The primary analyses will utilize a between-group design (CAPRI versus control groups) at six time points (each month)). Significant change in treatment delivery will be measured on the RDI ratio, calculated with the Morisky score and/or the Medication Event Monitoring System (MEMs) results. If distribution is normal, a student *t*-test will be used to compare RDI means, as well as secondary outcomes designed as continuous variables. If not, a Mann–Whitney test will be used. Chi2 or Fisher’s test will be used to compare secondary outcomes designed as binary variables. Baseline data will be examined to analyze probability of attrition bias.

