## Method/design

### Study setting

The proposed Randomized Controlled Trial is a large-scale trial designed to assess the impact of an innovative navigation program denoted CAPRI, that is based on two Nurse Navigators and a web portal and ensures coordination between community and hospital as well as between patients and navigators, within the context of routine delivery of oral anticancer therapies. The broad research aim is to assess (a) the program’s impact on oral therapeutic delivery for patients with metastatic cancer treated with oral chemotherapy and/or targeted therapy, and (b) CAPRI’s effectiveness in terms of the treatment’s toxic side effects, tumor response, Progression Free Survival, Overall Survival, patient quality of life and patient experience, and (c) the economic evaluation of the CAPRI program.

The study will evaluate the CAPRI’s efficacy in comparison with usual care. The RCT will randomize 1,000 individuals fulfilling inclusion criteria into either the CAPRI group or the control group, for a 6-month period (Fig. 1). Participant outcomes could be assessed at baseline (T0) and each month of intervention, excepted for quality of life (T1 – T6) and patient experience (T6). Control group participants will be offered the intervention when the CAPRI program ends for the intervention group.

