### Sample size calculation

Given previous research showing Relative Dose Intensity (RDI) varying from 60% to 95% for oral therapeutics in cancer care, considering a Relative Dose Intensity lower than 85% as a signal for reduced survivorship, and considering that a difference of 6% to 20% was found between different treatment options or between different cancer types, we expect a sizeable effect of the CAPRI program on patient RDI (5% difference with the control group) [29–32]. Therefore, 393 individuals per group will be sufficient to detect a difference in RDI between the CAPRI program and usual care, assuming significance is set at 5% (α = 0.05) power at 80% and a standard deviation of 25% for the distribution of mean change. We will include an additional 27% (*N* = 107 per group) to allow for attrition.

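### The primary analyses of RDI are placed at six monthly time points with no decisive one named, while the trial is sized for a single two-sided 5% test

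*Protocol article*

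**What the plan says.** Three sections of the protocol article bear on the primary comparison.

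- **Data analysis.** "The primary analyses will utilize a between-group design (CAPRI versus control groups) at six time points (each month". RDI means are then to be compared by a t-test, or by a Mann–Whitney test if the distribution is not normal. No model for repeated values, joint test, testing order or division of alpha is mentioned.
- **Primary endpoint.** "The primary endpoint of the study will be significant change in the delivery of oral treatment, measured by Relative Dose Intensity". RDI is the dose delivered over time relative to the prescribed dose intensity. No period or month is fixed for that ratio.
- **Sample size calculation.** The anticipated gain is 5 points of RDI over control, and on that basis "393 individuals per group will be sufficient to detect a difference in RDI between the CAPRI program and usual care". The other inputs listed there are an alpha of 0.05, 80% power and an SD of 25 points. A further 107 per group are added "to allow for attrition", giving 500 per group and the 1,000 patients followed for 6 months in the Study setting section.

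The monthly schedule also appears under Instruments of measurement, but as a data-collection schedule.

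**The concern.** The analysis section speaks of primary analyses, in the plural, at six time points. The tests it names are two-sample tests of one value per patient, and neither combines six repeated values into one comparison. Read as written, there are six comparisons of the primary endpoint, and nothing says which of them decides the trial.

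The sample size section assumes one comparison. The endpoint is itself worded as a significant change, which does not say when that change must be shown. The month that carries the primary claim could therefore be chosen after the results are seen, or a reader could fairly ask why a difference at one month and not at five others is called a success. The error rate and power attached to the trial's main conclusion depend on a rule that the text does not contain.

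**Working it through.** **Inputs from the document (Sample size calculation):** difference 5 points of RDI, standard deviation 25 points, alpha 0.05, power 80%, 393 evaluable per group. Sidedness is not stated. **From Data analysis:** six monthly comparisons.

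**Assumed, because the document does not give them:** the success rule, the correlation between the monthly test statistics, and, for power, the same 5-point effect at every month.

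**Step 1. Reproduce the plan's figure.**
n per group = 2 × (z₀.₉₇₅ + z₀.₈₀)² × SD² / difference²
= 2 × (1.960 + 0.842)² × 25² / 5² = 392.4, rounded up to 393.
This matches. A one-sided 5% test would give 310, so the plan was sized for one two-sided 5% test. Power at 393 is 80.1% by the normal approximation and 79.96% by the noncentral t.

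**Step 2. Success if any month is significant.** With six independent tests, 1 − 0.95⁶ = 0.265. Monthly RDI values in the same patients are correlated, so this is an upper figure. The correlated cases come from simulating six normal test statistics (2,000,000 draws), each tested at two-sided 5%:

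| Assumed structure | Chance of at least one false-positive month |
|---|---|
| Independent | 26.5% |
| Equal correlation 0.5 | 20.7% |
| Equal correlation 0.7 | 16.4% |
| Equal correlation 0.9 | 10.8% |
| Equal correlation 0.95 | 8.9% |
| AR(1), 0.5 | 23.5% |
| AR(1), 0.95 | 10.7% |
| RDI cumulative over independent months | 15.5% |

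The rate returns to 5% only if the six tests are perfectly correlated.

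**Step 3. Success only if all six months are significant.** The false-positive rate is then at most 5%. At 393 per group each test statistic has mean 5 / (25 × √(2/393)) = 2.80. The probability that all six exceed 1.96 was obtained by numerical integration over the shared component of equally correlated statistics:

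| Equal correlation | Power for all six |
|---|---|
| 0.5 | 47.9% |
| 0.7 | 56.7% |
| 0.9 | 67.6% |
| 0.95 | 71.5% |

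**Step 4. Keeping six tests with a Bonferroni split.** Alpha per test is 0.05 / 6 = 0.00833, with critical value 2.638. Power at each month is Φ(2.80 − 2.638) = 56.6% at 393 per group and 70.0% at 500 per group. Reaching 80% at each month needs 606 evaluable per group, more than the 500 to be randomised.

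**Step 5. One test of one quantity.** Alpha is 5%, and 393 per group gives 80% power, as the sample size section states.

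**The case against.** The best defence is that the six time points are only visits, and that the monthly data feed one cumulative RDI per patient, compared once. The endpoint definition refers to dose over time, the test is described in the singular, and the sizing is for one difference. This is also a condensed article, and the decisive time point and the handling of repeated measures are commonly left to the full protocol or analysis plan.

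Part of this stands. The single-comparison reading is possible, and may be what was intended. The text does not establish it, because the article attaches the six time points to the primary analyses and the endpoint definition sets no period. The point therefore concerns something the article does state and that disagrees with its own sizing.

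The defence is also right that no success rule is written down. A reader might infer that the trial's false-positive rate simply is 26%, or that success at any one month is the plan. The documents support neither. The any-month rule is a reading, independence is implausible for repeated values in the same patients, and an all-months rule would not inflate alpha at all.

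A reader might also infer that the later monthly comparisons would use only patients still alive and still contributing RDI, and so suffer selection after randomisation. The article states no analysis set and does not say how months after death or stopping are scored, so that cannot be held against it.

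**Conclusion.** The inconsistency is real and concerns the primary conclusion. The Data analysis section places the primary analyses at six months, whereas the sample size is for one two-sided 5% test.

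Its size is conditional. Under an any-month rule the false-positive rate is about 9% to 21% for assumed equal correlations of 0.95 down to 0.5. Under an all-months rule power is about 72% down to 48% over the same range, with a constant monthly effect. Under either rule, the stated 5% error rate and 80% power do not both describe the six-comparison analysis. They do hold for a single named comparison, provided the 5-point difference and 25-point standard deviation refer to that quantity.

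The finding is that the governing rule is absent and the sections conflict. It has not been shown that the trial's error rate is any particular figure above 5%.

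**What to change.** Reconcile the Primary endpoint, Sample size calculation and Data analysis sections:

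- Name one primary quantity per patient, RDI over the whole 6-month period.
- Compare it once between the randomised groups at two-sided 5%, in all randomised patients as allocated. Restricting the analysis to patients who started treatment would itself be an exclusion after randomisation.
- Fix in advance how months after death or stopping enter the ratio, and how the monthly Morisky and MEMs readings are turned into one 6-month value.
- Confirm that the 5-point difference and 25-point standard deviation apply to that 6-month RDI.
- Report the six monthly values descriptively, or from one repeated-measures model without separate significance claims.

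If cumulative RDI was always the intention, the change is mainly one of wording. In either case it needs no additional patients or visits, and 393 per group with 80% power stands. The price is that the sponsor gives up claiming success at a single month. Keeping six separately tested months with a Bonferroni split would cost far more, at 606 evaluable patients per group.

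### The primary RDI analyses are placed at six monthly time points, but the sample size, 5% level and 80% power describe one comparison that the article never identifies

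*Protocol article*

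**What the plan says.** All references are to the protocol article.

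- **Data analysis:** "The primary analyses will utilize a between-group design (CAPRI versus control groups) at six time points (each month"). The tests named for RDI are Student's t-test if the distribution is normal and Mann–Whitney if not. No repeated-measures model, summary over months, deciding month or adjustment across months is given.
- **Primary endpoint:** "The primary endpoint of the study will be significant change in the delivery of oral treatment", measured by RDI. RDI is defined as a ratio of delivered to prescribed dose over time, with no window or month attached. The section carries one hypothesis, an increase in RDI over control.
- **Sample size calculation:** "we expect a sizeable effect of the CAPRI program on patient RDI (5% difference with the control group"), again without a time point. It states that "393 individuals per group will be sufficient to detect a difference in RDI between the CAPRI program and usual care". The level behind that number is a single 5%, and the remaining inputs are "power at 80% and a standard deviation of 25"%.
- **Instruments of measurement and Table 2:** RDI is collected monthly during the 6-month programme.

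**The concern.** A sample size, a significance level and a power figure belong to a particular test. Here they belong to one test of one mean difference, while the analysis section labels as primary a set of comparisons at six occasions. The tests named do not combine six repeated values from the same patient into one result, so on a plain reading there are six monthly results.

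The primary endpoint is framed as a significant change, and nothing says how six results become one conclusion. The choice could therefore be made after the data are seen, and it decides what the error rate and power of the primary claim are. The issue is separate from missing data: it would exist even if every patient stayed on treatment and in follow-up.

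**Working it through.** **Inputs from the article.** Difference 5 percentage points, SD 25, alpha 0.05, power 80%, 393 per group, six monthly time points. Sidedness is not stated.

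**Inputs assumed.** The correlation between a patient's monthly RDI values is not given; I used 0 to 0.9. Unless marked otherwise the correlation is exchangeable (the same between any two months). Test statistics are treated as normal.

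**1. Reproduce the plan's figure.**
n per group = 2 × (1.960 + 0.842)² × 25² / 5² = 392.4, so 393. A one-sided 5% test would give 310, so two-sided is inferred from the match. Power at 393 is 80.1%. The stated N is correct for exactly one test.

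**2. If any one of six unadjusted 5% tests could count as success.**
Independent months: 1 − 0.95⁶ = 0.265. This is an upper bound, because correlation between two-sided normal tests can only lower it. With correlation, by simulation of six jointly normal statistics under no effect:

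| Correlation | Exchangeable | AR(1) |
|---|---|---|
| 0 | 26.5% | 26.5% |
| 0.5 | 20.7% | 23.5% |
| 0.7 | 16.4% | 19.9% |
| 0.8 | 13.8% | 17.2% |
| 0.9 | 10.8% | 13.3% |

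The risk is above 5% throughout.

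**3. If all six months had to be significant.**
With a true 5-point difference in every month, the expected test statistic at 393 per group is 5 / (25 × √(2/393)) = 2.80. Power for six out of six is 26% at correlation 0, 48% at 0.5, 62% at 0.8 and 68% at 0.9 (AR(1): 39% at 0.5, 62% at 0.9). The false-positive risk is then far below 5%, but the 80% power is lost.

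**4. If alpha were adjusted across the six months.**
- Bonferroni, 0.05/6 = 0.00833, critical value 2.638. Power for a given month at 393 is Φ(2.804 − 2.638) = 56.6%. For 80% in a given month, n = 2 × (2.638 + 0.842)² × 25² / 5² = 605.5, so 606 per group.
- Holm, with an equal effect in all months: about 65–68% per month over correlations 0 to 0.9 (simulated).
- Bonferroni, power for at least one significant month: about 90% at correlation 0.5, 83% at 0.7, 78% at 0.8 and 72% at 0.9.

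**5. If one comparison is named.** Step 1 applies unchanged: 393 per group, two-sided 5%, 80.1% power.

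**The case against.** **The article does not say that six tests will each be declared at 5%, or that any month suffices.** This is right. The six time points and the t-test stand in different sentences, and the success rule is an inference. A reader might conclude that the trial's 5% error rate is certainly not delivered. The documents do not support that; they leave the rule open. The percentages in step 2 describe one literal reading.

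**A one-test reading is available.** RDI is defined over time, there is one hypothesis, and the monthly visits could simply be when data are collected. That reading is possible and would reconcile the sections. But no section adopts it, and the analysis section, which places the primary analyses themselves at six time points, points the other way. If a cumulative value is meant, the same sentence still needs correcting.

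**Alpha allocation belongs in the statistical analysis plan.** Silence on it would be no finding. Here the article makes a positive statement about the primary analyses that does not match its own sample size. An analysis plan naming one test would be changing that statement.

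**Adjusting alpha need not cost power.** This partly stands. A reader might infer that splitting alpha necessarily takes power below 80%. That is true for a claim about a given month. For at least one significant month, Bonferroni keeps power above 80% up to a correlation of about 0.7.

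**The power figures use 393.** This also stands. Early months may have closer to the 500 per group randomised, where Bonferroni power for a given month is 70.0%.

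**Conclusion.** The point holds as a mismatch between the stated primary analysis and the stated design parameters. The 393 is not wrong; it is right for one two-sided comparison that the article does not identify.

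Under the any-month reading the false-positive risk is about 11% to 21% for exchangeable correlations of 0.9 down to 0.5, and never above 26.5%. Independence is implausible for one patient's successive monthly values, so 26.5% is a bound and not an expectation. Under the all-months reading power is about 48% to 68% over the same correlations, if the effect is 5 points in every month. These sizes rest on assumed correlations and on a success rule that the article does not state. The mismatch itself rests on neither.

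It should be settled before outcome data are compared by arm, because a choice of month made afterwards cannot be undone.

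**What to change.** In the Primary endpoint and Data analysis sections, name one primary RDI comparison. One suitable form: the difference between arms in one RDI value per patient covering the 6-month period, tested two-sided at 5% and reported with its 95% confidence interval. A single named month or one joint longitudinal test would also give one primary test, provided the sample size assumptions are confirmed for it. State that the six monthly comparisons are descriptive and support no separate claim. Add to the Sample size calculation that the test is two-sided and that the 5-point difference and SD of 25 refer to the named comparison; 393 per group and 80% power then stand on those inputs.

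If month-specific claims are to be kept, adjust across the six months and state the power for the method chosen: at 393 per group, about 56–57% per month with Bonferroni, or about 65–68% with Holm under an equal effect in all months.

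The cost is a sentence or two, with no new data and no more patients. The sponsor gives up the option of claiming success on a single month.
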